### Clinical data collection

2.3.

All INSIS sites will transfer the raw data from their database to the INSIS REDCap database, which is designed to capture general common data elements for all participants including age, country of enrollment, biological sex, self-reported gender, COVID-19 vaccination details, relevant past medical history, relevant medications, and details of the AEFI/condition including interval from vaccination to symptom onset (if applicable), specific symptoms, and diagnostic results. Details of the AEFIs will be captured in forms derived from the Brighton Collaboration Case Definitions for TTS/VITT and myocarditis/pericarditis to ensure each case is evaluated using consistent criteria. At each follow-up visit, data will be collected on any changed signs or symptoms including those associated with myocarditis, pericarditis, or TTS/VITT to detect persistent or recurrent disease activity.

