#### Sample collection and processing

2.4.4.

Both cases and controls will undergo data and sample collection for multi-omics analyses, including transcriptomics, proteomics, and metabolomics using a standardized protocol. Samples will be captured as close to the onset of an AE as possible, up to 12 weeks after the event, with follow-up samples collected as needed. Participants will also be invited to consent to saliva or blood sampling for DNA extraction and genotyping under the GVDN genomics protocol.

Sample collection for cases and controls will be conducted using retrospective residual clinical samples or prospectively at selected sites. At each timepoint (see Table 1), peripheral blood (5–15 ml) will be collected according to protocol. Where processing facilities are available, whole blood (20–30 ml) will be collected for PBMC isolation. Additional sample types, including serum, may be collected according to site-specific or study-specific protocols (refer to INSIS Study SOP in supplementary file 1). Samples for multi-omics analysis will be stored at the participating site until they are ready to be shipped on dry ice or liquid nitrogen to an INSIS laboratory with biobanking facilities, such as the Precision Vaccines Program (PVP), where they will be stored at −80 °C until analysis (Fig. 2). As of May 15, 2025, 7 sites have entered data for 154 cases and 110 controls into the INSIS REDCap database, with >1100 samples (including serum, plasma, PBMC, and saliva) recorded in the INSIS REDCap database. Additionally, > 1600 sample aliquots have been entered into the Laboratory Data Management System (LDMS) [41] sample management system. These numbers will continue to increase as sites enter their data into the INSIS REDCap and LDMS databases.

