#### Untargeted mass spectrometric profiling

2.5.1.

Proteomics will be performed ([name] Lab, Boston Children’s Hospital; Boston, MA) employing a two-pronged approach [42]. First, the plasma proteome will be quantitatively mapped without any depletion considering the important immunomodulatory roles of a sizable fraction of the standard depletion targets such as immunoglobulins and complement pathway components [43,44]. Mapping the vaccine and AEFI-associated changes in abundance for these proteins is important for understanding the pathophysiological processes of these AEFIs. To map the ‘classical’ plasma proteome, the neat plasma will be processed in a high throughput fashion. To map the ‘tissue leakage’ plasma proteome, we will deplete the most abundant plasma samples using perchloric acid, which can be conducted in a high-throughput and cost-efficient manner on thousands of samples [45-47].

The two resulting plasma protein digests will be analyzed by LC-MS in discovery mode using a high-throughput sample delivery and high-performance liquid chromatography (HPLC) system (Evosep One) front-end and a Bruker ion mobility/quadrupole/TOF mass spectrometer (timsTOF HT) back-end to ensure robustness. The instrument will be operated in Data Independent Acquisition (DIA) mode to ensure maximum completeness of the data. All data will be qualitatively and quantitatively analyzed using the Bruker ProteoScape hard- and software environment.

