### Hormone analysis

2.6.

Considering the higher incidence of myocarditis in males post SARS-CoV-2 infection and vaccination, it has been suggested that androgens may play a potential role in post-COVID-19 vaccination cardiac events [56]. Furthermore, extensive research has been conducted on the impact of androgens on the immune system [57].

Steroid hormone measurement will be conducted on suitable plasma and/or serum samples using liquid chromatography coupled to tandem mass spectrometry (LC-MS/MS). Such analysis will be conducted (Clinical Biochemistry Laboratory, Department of Diagnostic Medicine of the I.R.C.C.S. Bambino Gesù Children’s Hospital) using the Xevo TQ-Smicro Mass Spectrometer of Waters. Sample preparation will be carried out using the CE-IVD certified diagnostic kit of Chromsystems (Munich, Germany) (or equivalent), and samples will be processed on an appropriate platform such as a mass spectrometer equipped with an ACQUITY UPLC I-Class liquid chromatograph that allows the realization of an ultra-high performance and low dispersion liquid chromatography optimized to derive maximum benefits in terms of resolution and sensitivity, and a triple quadrupole that complies with Directive 98/79/EC in all its parts. This type of instrumentation couples ultra-high-performance, low-dispersion chromatography with triple quadrupole used in Multiple Reaction Monitoring (MRM) mode, a specific method developed to detect specific peptides in complex biological mixtures such as human plasma and serum.

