### Integrated multi-omics analysis

3.5.

Multi-omics data from patients with well-defined phenotypes (e.g., Brighton level 1 TTS/VITT) and controls will be analyzed using data integration approaches such as MultiOmics Factors Analysis (MOFA) and Data Integration Analysis for Biomarker Discovery using Latent Components (DIABLO) as previously described [84,85]. MOFA is a computational method used to integrate and analyze multi-omics datasets which distinguishes between patterns that are shared across different omics layers and those that are specific to individual layers [84]. DIABLO identifies key drivers associated with the response variable of interest across all input data matrices jointly. Cross-validation will determine the optimal model hyperparameters (number of components, features per component) and estimate the model’s ability to generalize to new data. Selected model features will undergo pathway over-representation analysis against the Reactome pathways database (via MSigDB) and blood transcriptional module (BTM) annotated gene set libraries, with *p*-values adjusted to control false discovery rate (FDR).

Multi-omics data will be compared within groups over time (e.g., myocarditis/TTS/VITT onset vs post-recovery) and between cases and controls to identify differences in basal levels of analytes in cases (using baseline samples: pre-vaccination, post-recovery/ ≥3 months postvaccination), as well as at time of myocarditis/TTS/VITT diagnosis (and similar timepoints post-vaccination in controls). Analyte levels in blood/plasma will also be compared to normal ranges in adults where available. Two-way comparisons will be performed between cases and healthy controls vs cases and controls with non-vaccine associated myocarditis or HIT.

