* Participants may be included if multi-OMICs samples are available from only 1 timepoint but 2 or more timepoints are preferred within these approximate timeframes (preferably an acute sample and follow up sample). In some cases an early follow up sample and late follow up sample (e.g., 3 and > 6 months) will be acceptable. A maximum of 90 ml of blood will be drawn on children <16 years of age.

† At time of first specialist assessment (e.g., cardiology, special immunization clinic).

‡ If not consented at presentation, consent will be obtained at time of specialist assessment for retrieval of residual serum/plasma from initial presentation.

** Aim for 3–7 days post-vaccination for controls matched to myocarditis cases; 5–42 days post-vaccination for controls matched to VITT cases, longer timeframes may be appropriate for additional AEFI of interest.

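### Acute case samples may be drawn after treatment has begun, and the section 3.5 contrasts do not separate treatment from disease

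*Protocol article*

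**What the plan says.** **Sampling.** Section 2.4.4 sets the case draw by distance from the event: "Samples will be captured as close to the onset of an AE as possible, up to 12 weeks after the event". The footnotes to Table 1 add: "Participants may be included if multi-OMICs samples are available from only 1 timepoint but 2 or more timepoints are preferred". They also say: "In some cases an early follow up sample and late follow up sample (e.g., 3 and > 6 months) will be acceptable". Table 1 places the second prospective draw at 2–8 weeks, at the first specialist assessment. None of these rules refers to the start of treatment.

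**Contrasts.** Section 3.5 states: "Multi-omics data will be compared within groups over time (e.g., myocarditis/TTS/VITT onset vs post-recovery) and between cases and controls". That sentence goes on to a comparison of basal levels, using pre-vaccination or post-recovery samples, and to a comparison at diagnosis against controls at similar times after vaccination. The section also compares cases with non-vaccine myocarditis or HIT controls.

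**Matching.** Section 2.4.3 matches on age, sex, ancestry and vaccine. It asks that disease controls have samples from their clinical presentation.

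**Treatment.** The Introduction credits earlier diagnosis and treatment with lower VITT fatality. Section 2.1 places investigation of cases within routine care. Section 2.3 captures "relevant past medical history, relevant medications, and details of the AEFI/condition". For patients not consented at presentation, a Table 1 footnote provides that "consent will be obtained at time of specialist assessment for retrieval of residual serum/plasma from initial presentation".

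**The concern.** A healthy control without an adverse event had no event to be treated for. A case may be on treatment at the draw and off it at recovery. Disease, treatment and phase can then move together in the case-versus-healthy contrast and in the onset-versus-recovery contrast. An analyte moved only by a drug would look like a mechanism, and a disease signal that a drug suppresses could be missed.

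Some assays are directly exposed if the relevant drugs are given. Section 2.5.1 leaves plasma undepleted because of the "important immunomodulatory roles of a sizable fraction of the standard depletion targets such as immunoglobulins and complement pathway components", so infused immunoglobulin would be measured as the patient's own. The antigen array in section 2.7 reads bound antibody and has the same problem. In section 2.6, "Steroid hormone measurement will be conducted on suitable plasma and/or serum samples", so an administered steroid hormone would bear on the readout itself. At stake is the study's stated product, actionable biomarkers.

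**Working it through.** **Nothing to reproduce.** The article states no sample size, alpha, effect size or treatment frequency on this point. What follows is an illustration of the possible range, not an estimate for this study.

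**Inputs**
- Counts: 154 cases and 110 controls (section 2.4.4), all events and control types pooled. A 50 v 50 single-event subset is an assumption.
- f, the share of case samples drawn on treatment: assumed 0.25 to 0.9.
- d, the drug's shift of an analyte in SD units: assumed 0.3 to 1.0.
- Two-sided levels of 0.05, 0.001 and 0.00005. The last is 0.05/1000, for an assumed 1,000 analytes.

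**Formulas, for an analyte with no disease effect**
- Expected case-control difference = f × d. The onset-versus-recovery difference is also f × d if patients are off drug at recovery.
- SE = √[(1 + f(1−f)d²)/n_case + 1/n_control]
- Chance of flagging = Φ(f × d/SE − z), with z = 1.960, 3.291 and 4.056 for the three levels. This counts flags in the drug's direction only.

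**Worked row.** f = 0.5, d = 1, 154 v 110: SE = √(1.25/154 + 1/110) = 0.131, and 0.50/0.131 = 3.81. The chances are Φ(1.85) = 0.968, Φ(0.52) = 0.699 and Φ(−0.24) = 0.404.

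| f | d | f × d | 154 v 110: chance at 0.05 / 0.001 / 0.00005 | 50 v 50: same levels |
|---|---|---|---|---|
| 0.25 | 0.3 | 0.075 | 0.087 / 0.004 / <0.001 | 0.056 / 0.002 / <0.001 |
| 0.5 | 0.5 | 0.25 | 0.507 / 0.095 / 0.019 | 0.233 / 0.020 / 0.002 |
| 0.5 | 1.0 | 0.50 | 0.968 / 0.699 / 0.404 | 0.654 / 0.175 / 0.045 |
| 0.9 | 1.0 | 0.90 | 1.000 / 1.000 / 0.999 | 0.993 / 0.867 / 0.635 |

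The bias f × d does not shrink as recruitment grows, while the SE does, so more samples make the false signal more certain.

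**Do the stated safeguards remove it?**
- *FDR control and cross-validation* (section 3.5) deal with chance and overfitting. A systematic shift is present in every fold.
- *Randomising samples for each assay* (section 3.2) balances assay runs. It leaves treatment tied to case status.
- *Disease controls* help to the extent that they are treated alike at the draw. Section 2.4.3 wants theirs from presentation, while a case sample may be up to 12 weeks later. HIT controls are, by the name of the condition, heparin-exposed.
- *Residual presentation samples* are serum or plasma only. They cannot serve the PBMC assays (RNA sequencing, CyTOF, methylation), and their own treatment status is not stated.
- *Recorded medications* make a fix possible, but the article does not tie them to the time of the draw or to any contrast.

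**The case against.** The strongest reply is that this is a condensed article. Covariates and sensitivity sets commonly sit in an analysis plan, none is shown here, and section 3.5 describes its methods only as examples. That stands: absence of adjustment is not by itself a finding. What remains is the sampling rule and the contrasts, which are stated. A treatment covariate would still need dates tied to draws. Because only cases are treated for the event, it would make the case-versus-healthy estimate rest on the pre-treatment cases.

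Second, the acute contrast is set at diagnosis, no text assigns the 2–8 week draw to it, and one contrast uses baseline samples away from the acute phase. This also stands, and it narrows the point to the two acute contrasts. It does not clear them, because the plan accepts a single timepoint or follow-up samples alone and does not say which draws count as diagnosis.

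Third, a reader might infer that drug effects will be reported as biomarkers, or that treatment coincides almost perfectly with being a case. The documents do not support either. They give no treatment rate, agent or timing for cases, and retrieved presentation samples may precede treatment. That healthy controls are untreated is likewise an inference from their having had no adverse event.

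Fourth, restricting to pre-treatment samples discards data in a rare-event study and may select by care pathway. That is a fair reason not to make it the only analysis for every assay.

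**Conclusion.** The concern holds in a limited form. The plan permits post-treatment acute samples and sets them against healthy controls and against the patient's own recovery sample, so treatment effects may be mistaken for disease biomarkers. The stated safeguards reduce this only in part.

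Its size is not derivable. Across the assumed inputs, with the pooled counts, the chance of flagging a treatment-only analyte runs from 0.087 to 1.000 at 0.05, and from below 0.001 to 0.999 at 0.00005: negligible to near certain. These figures assume univariate comparisons, equal residual variance and no disease effect on the analyte. They do not model MOFA or DIABLO. The finding rests on the stated sampling rules and contrasts, not on any one row of the table.

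**What to change.** In section 3.5, with a supporting data field under section 2.3:

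1. Record treatment start relative to each blood draw, and classify every case and disease-control sample as pre- or post-treatment by drug class.
2. Report the acute case-control and onset-versus-recovery contrasts stratified by that flag. Add a pre-treatment-only analysis: at least as a pre-specified sensitivity analysis, and as the main analysis for serum and plasma assays where numbers allow.
3. Compare cases with disease controls within the same treatment stratum.
4. Call a feature an AEFI biomarker only if its direction and approximate size persist in pre-treatment samples.
5. Leave samples taken after any infused immunoglobulin out of the antigen-array and immunoglobulin-proteome analyses, and samples taken on exogenous steroid hormones out of the hormone analysis.

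**Cost.** Medication dates must be retrieved across sites, partly in retrospect, and the pre-treatment strata are smaller. If half of the 154 cases were pre-treatment, the SE against 110 controls would be √(1/77 + 1/110) = 0.149, compared with √(1/154 + 1/110) = 0.125 for all cases with no drug shift, about 19% wider. If only a tenth were (15 cases), it would be √(1/15 + 1/110) = 0.275, about 2.2 times as wide. PBMC assays will feel this most, because retrieved presentation samples supply no cells. Strata may also differ in severity, so differences between them should not be read as drug effects. Patient care and study procedures do not change.

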VITT has been linked to adenoviral vector COVID-19 vaccines (e.g., ChAdOx1 and Ad.26.COV-2.S). First reported in March 2021, VITT is characterized by rapidly progressive thrombosis, particularly in cerebral venous sinuses and splanchnic circulation veins, accompanied by thrombocytopenia and markedly elevated D-dimer and anti-platelet factor 4 (PF4) antibodies driving platelet activation [11-15]. The incidence of VITT ranges from 0.1 to 1.2 cases per 100,000 vaccinations following Ad26.COV-2.S and 1 to 5 per 100,000 following the first dose of ChAdOx1 vaccine [16]. Early diagnosis and treatment have reduced case fatality rates from as high as 40 % to 13–15 % [17].

Myocarditis and pericarditis emerged as safety signals following the rollout of COVID-19 mRNA vaccines. Although these vaccines have been pivotal in controlling the pandemic, there is an increased incidence of myocarditis and pericarditis, particularly among young males aged 12–29 years after the second dose [18,19-25]. Initial data suggested most patients appeared to recover quickly. Ongoing studies are focused on determining long-term outcomes, including resolution of cardiac MRI changes and cardiac-specific biomarkers, with some studies reporting persistence of MRI changes and symptoms in a subset of patients [26]. Importantly, despite these rare events, the benefits of COVID-19 vaccination in preventing severe disease, hospitalization, and death continue to far outweigh the risks. The mRNA platform is now being used to develop vaccines against a range of other diseases including influenza, Respiratory Syncytial Virus (RSV), Nipah, and Lassa fever, as well as for non-infectious indications such as cancer [11,27].

Myocarditis and pericarditis have also been reported following non-mRNA COVID-19 vaccines, including the adjuvanted protein subunit vaccine Novavax NVX-CoV2373 and AstraZeneca’s ChAdOx1 [23]. Early studies suggest that the spike protein may contribute to these rare cardiac events [28,29]. Ongoing research into the underlying biological mechanisms is essential to refine our understanding of vaccine safety. Continued surveillance and investigation are critical to ensuring public confidence and the safety of vaccination programs.

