#### Case-control matching

2.4.3.

Cases will be matched to healthy controls, recruited through observational vaccine studies and other approaches, who received the same vaccine platform and, where feasible, the same product (e.g., BNT162b2 or mRNA-1273) and did not develop an AEFI. Samples from these controls will be matched to cases at a ratio of at least 1:1 and ideally 3:1 for multi-omics analysis by age group, biological sex, vaccine type, and ancestry.

Cases may also be frequency matched to controls with a non-vaccine-associated TTS/VITT-like condition (e.g., heparin-induced thrombocytopenia [HIT]) or non-vaccine-associated myocarditis or pericarditis, who meet Brighton criteria and have samples collected and stored at the time of their clinical presentation. Matching will be done by age (±5 years), biological sex, ancestry (where possible), and vaccine received (for healthy controls).

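### The supplementary comparison with adult normal ranges is not limited to adults, although children under 16 are sampled, so age-dependent analytes in minors can be misread

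*Protocol article*

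**What the plan says.** Section 3.5 (Integrated multi-omics analysis) of the protocol article plans comparisons within groups over time and between cases and controls. It then adds: "Analyte levels in blood/plasma will also be compared to normal ranges in adults where available". No paediatric or age-specific range is mentioned there, and nothing says whose levels are compared.

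Three other places bear on who is measured and what is measured:

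- **Table 1, footnotes (multi-omics sampling schedule):** "A maximum of 90 ml of blood will be drawn on children <16 years of age".
- **Section 1 (Introduction):** the increased incidence of myocarditis and pericarditis after mRNA vaccination is described as falling "particularly among young males aged 12–29 years after the second dose".
- **Section 2.6 (Hormone analysis):** "Steroid hormone measurement will be conducted on suitable plasma and/or serum samples". The rationale is that "androgens may play a potential role in post-COVID-19 vaccination cardiac events".

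Section 2.4.3 (Case-control matching) describes the main comparison group: healthy vaccinated controls are matched at a minimum of 1:1 and "ideally 3:1 for multi-omics analysis by age group, biological sex, vaccine type, and ancestry".

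**The concern.** A reference range shows whether a level is unusual only if it was built on people like the one being measured. Where the healthy level of an analyte differs between adolescents and adults, a 13-year-old's position against adult limits partly reflects age. Two errors follow. A healthy minor can fall outside the adult range, and a minor with a real deviation can fall inside it.

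Adolescents are not a marginal group here, because the age band in which the Introduction places the cardiac events starts at 12. Steroid hormones are the clearest example of an analyte class for which an age difference is plausible. At stake is the reading of this one comparison in minors: a level reported as abnormal, or as normal, for a reason unrelated to the adverse event.

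**Working it through.** The plan states no figure on this point, so there is none to reproduce. The check has two parts.

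**1. Reading the passages together**

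- In Section 3.5 the words about adults describe the ranges, not the participants. The qualifier on availability limits which analytes have a range, not whose levels are compared.
- The blood-volume footnote belongs to Table 1, the schedule for prospectively enrolled cases and controls in the multi-omics analysis. Children under 16 are therefore expected to give the samples that Section 3.5 analyses.
- Followed as written, the comparison sets minors' levels against adult limits.

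**2. Illustration of size**

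Assumptions, none of them from the documents:

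- The analyte is normally distributed with the same SD in healthy adults and healthy minors.
- The adult range is the central 95%, that is mean ± 1.96 SD.
- The healthy mean in minors differs from the adult mean by *s* adult SD.

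*Healthy minors outside the adult range:* share = Φ(−1.96 − s) + 1 − Φ(1.96 − s). The direction of the shift does not matter here.

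For s = 1: Φ(−2.96) + 1 − Φ(0.96) = 0.0015 + 0.1685 = 0.170.

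*True elevation missed:* take a minor whose healthy mean lies *s* SD below the adult mean and whose level is truly raised by 2 SD on the own-age scale. The chance of exceeding the adult upper limit is 1 − Φ(1.96 − (2 − s)). Against an own-age range it is 1 − Φ(1.96 − 2) = 0.516.

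| Assumed shift s (adult SD) | Healthy minors outside adult range | True +2 SD rise above adult upper limit |
|---|---|---|
| 0 (own-age range) | 5.0% | 51.6% |
| 0.5 | 7.9% | 32.3% |
| 1.0 | 17.0% | 16.9% |
| 1.5 | 32.3% | 7.2% |
| 2.0 | 51.6% | 2.5% |

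Both errors grow quickly with the shift. The documents give neither the shifts nor the age distribution of the 154 cases and 110 controls entered so far, so the number of participants affected cannot be stated.

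**The case against.** The strongest defence is that the sentence is a descriptive addition and may be meant for adult participants only. The article defines no in-range/out-of-range variable and no test based on ranges. Several platforms give no clinical range at all: the Olink T96 panel reports relative values, and the mass-spectrometric proteomics and the metabolomics are untargeted.

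Most of this stands, and it limits the reach of the point to age-dependent analytes that have a range. The adults-only reading is possible, but the sentence does not say so, and the blood-volume footnote shows that minors are sampled. The article states a particular comparator that does not suit part of its own population. This is not a detail that a condensed article has merely left out.

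A reader might go further and infer three things that the documents do not support.

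- *That the androgen hypothesis is distorted.* Section 2.6 does not tie that hypothesis to a reference range, and it can be examined against controls matched on age group and sex.
- *That the age caliper adds to the problem.* The relevant words are "Matching will be done by age (±5 years), biological sex, ancestry (where possible), and vaccine received (for healthy controls". They close the paragraph on frequency matching to disease controls, where individual pairs need not exist. Any figure for added noise within pairs would rest on an assumed hormone trajectory and an assumed age mix.
- *That the lack of a stated continuous age term in the hormone analysis is a defect.* A journal article commonly leaves such model detail to the full protocol or analysis plan. Age is collected under Section 2.3.

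**Conclusion.** The point holds within limits. The adult-range comparison in Section 3.5 is unsuitable for minors as written, and the documents show that minors are sampled. For age-dependent analytes with a reference range, such as steroid hormones, it *can* make healthy adolescent levels look abnormal or conceal true deviations. It would be too strong to say that it *will*, because no flagging rule is defined and no age difference is quantified.

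Under the normal model with equal SDs, assumed shifts of 0.5, 1 or 2 adult SD raise the share of unaffected minors outside the range from 5% to 8%, 17% or 52%. That hormones or other analytes shift by any such amount is an assumption.

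The planned inferences do not depend on this comparison. The matched case-control contrasts and the within-person comparisons over time are unaffected. This is a correction to a supplementary analysis, worth making because it is simple and removes an avoidable artefact in an age group central to the myocarditis question.

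**What to change.** Replace the sentence in Section 3.5 with wording to this effect:

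> Where published normal ranges exist, levels will additionally be set against ranges specific to age and sex. Adult ranges are applied only to adult participants. For minors without a published range, the study's healthy vaccinated controls, matched on age group and sex, serve as the reference.

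No new data are needed: age and biological sex are common data elements in Section 2.3, and matched healthy controls are already planned in Section 2.4.3. The cost is one sentence of text. The downside is that fewer analytes will have a published range for minors. For those without one, the reference rests on however many matched young controls the study recruits, so its limits may be imprecise.
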